### ***Permitted local variations to the PASTA pathway***

Due to pre-existing variations in standard care clinical pathways and underlying healthcare service structures, there will be permitted variations in the different stages of the PASTA pathway as shown in the table below.

| PASTA component | Core content expected to be delivered                                                                                                                 | Local variation permitted                                                                                                                                                                         |
|------------------------|--------------------------------------------------------------------------------------------------------------------------------------------------------------|----------------------------------------------------------------------------------------------------------------------------------------------------------------------------------------------------------|
| Information            | Must use PASTA format.                                                                                                                                       | Any clinical information collection system (paper/electronic)                                                                                                                                            |
| Pre-notification       | Must be performed for all PASTA admissions.                                                                                                                  | Paramedic call to ED.
Paramedic call to ASU.
Dispatch call to ED.
Dispatch call to ASU.
Pre-notification may or may not include patient identifiable information.                            |
| Handover               | Must follow FASTA PASTA CT format.                                                                                                                           | Occurs in most suitable area for rapid handover and registration.
Receiving hospital team are ED and/or stroke service clinicians.
May include other relevant information for individual patients. |
| Scan                   | Paramedic assists with transfer to scan if <15minutes since handover.                                                                                        | Any appropriate hospital clinician accompanies patient.
Any brain imaging modality which would assist treatment decisions.
Transfer by ambulance or hospital trolley as long as no delay incurred. |
| Assist                 | Patient transferred off ambulance trolley onto hospital trolley.
Paramedic offers assistance for initial tasks.
Ambulance crew prepares for departure. | Team may not require assistance for each or all of tasks.
Ambulance operational conditions may shorten paramedic stay.                                                                                |
| Checklist              | Paramedic enquires about progress from any hospital team member at 15 minutes since handover.                                                                | Checklist completion should reflect usual local service procedures (e.g. telemedicine specialist review)                                                                                                 |
| Feedback               | Paramedic seeks feedback about provisional diagnosis and onset time.                                                                                         | Any member of hospital team can provide feedback.
Paramedic can seek feedback on any aspect of the assessment.
The hospital team may not (yet) be able to provide feedback.                        |

### ***Clinical deterioration***

During the pre-hospital phase of the PASTA pathway, if the patient's condition deteriorates then the paramedic will re-evaluate whether it is still appropriate to continue with the pathway according to their professional judgement and standard clinical protocols. The reason for any deviation will be recorded including the anticipated clinical scenarios of falling conscious level, seizure, hypotension and hypoglycaemia.

## ***Stroke mimic conditions***

Early identification of stroke patients is challenging because other conditions (“stroke mimics”) can create similar symptoms through different mechanisms e.g. unwitnessed epileptic seizures and migraine. In clinical practice approximately 20% of patients who are FAST positive receive a stroke mimic diagnosis following admission to hospital, brain imaging and stroke specialist review. Thrombolysis treatment would be inappropriate. If a stroke mimic condition becomes apparent during the initial hospital review, the hospital team will discontinue the thrombolysis assessment process as per standard clinical care.

### **10.2 Standard stroke care (comparison group)**

Patients in the comparison group will receive standard stroke care as per current local ambulance and hospital clinical protocols, which are reinforced by national clinical guidelines and audit. The study will not provide comparison group paramedics with additional training or documentation to support information collection, clinical communication or processes after hospital arrival.

The local thrombolysis assessment and treatment processes in hospital will not be deliberately altered. It is routine practice that all patients receiving thrombolysis are observed for at least 24 hours and undergo repeat CT brain imaging at 24-48 hours to exclude intracranial haemorrhage. Recognised complications of thrombolysis include allergic reactions (angioedema), extra-cranial haemorrhage and intracranial haemorrhage causing symptomatic neurological deterioration (defined as with an increase in NIHSS  $\geq 4$  points within 36 hrs of thrombolysis associated with parenchymal haemorrhage on repeat brain imaging)[24].

Whether or not they receive thrombolysis, all patients with acute stroke should be admitted to an ASU within 4 hours of hospital arrival in order to receive specialist assessment and care tailored to their individual needs. The overall length of stay in hospital reflects pre-morbid conditions and dependency, stroke severity and subsequent medical complications (e.g. pneumonia, thromboembolism, stroke recurrence), progress during rehabilitation, personal social circumstances and the local availability of services to provide further rehabilitation and care in the community (including generic and stroke-specific early supported discharge teams and community rehabilitation teams).

## **11. Study participants**

Intervention group paramedics will be asked to deliver the PASTA pathway to the following patients:

- Aged 18 years and over.
- Face Arm Speech Test (FAST)[9] positive or any presentation of new focal neurological symptoms which indicate acute stroke in the paramedic's clinical judgement.
- Within 4hrs of last known to be without new stroke symptoms in the paramedic's judgement.
- Admission to a study hospital

Patients will be identified and approached about enrolment in the study after arrival at hospital (see section 12 below). Patients approached about enrolment will meet the following criteria:

- Travelled to hospital with a study paramedic
- Aged 18 years and over
- Hospital specialist diagnosis of stroke
- Within 4 hours of stroke onset (onset time determined by the hospital stroke team) when assessed by the study paramedic

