**v. Assist:** If the CT scan is not immediately available, the hospital team will continue with urgent care of the patient according to the local service protocol and the patient will be transferred onto a hospital trolley. If ambulance service operational conditions are suitable and the hospital team require assistance, the paramedic can assist with the following tasks: insertion of an intravenous cannula if not already inserted, determining the patient's weight from assisting with transfer onto measurement scales or contributing towards a team estimation of weight, and repetition / clarification of clinical information (e.g. repeating the handover to a member of the stroke team). If the scan becomes available within 15 minutes of handover, the paramedic will assist with the patient transfer as above.

**vi. Checklist:** At 15 minutes after handover the paramedic will ask a member of the hospital team to confirm progress with key tasks: the status of the emergency brain scan request (if not yet performed) and stroke specialist review, confirmation of relevant medical history and medications, and ordering blood tests for clotting indices if relevant.

**vii. Feedback:** After completion of the checklist, the paramedic will request feedback from a hospital clinician about the provisional pre-hospital diagnosis of stroke, the estimation of onset time and any other aspect of the assessment process.

**viii Completion:** After seeking the checklist and feedback information the paramedic will complete and sign the study documentation. One copy will be retained at the hospital and a further copy will be returned to the ambulance service. The paramedic will depart as per usual operational procedure. This will be within 15-30 minutes of hospital arrival and therefore compliant with NHS Commissioning Board guidance for ambulance to hospital handover of emergency admissions[23].

The paramedic will record a reason if study documentation is signed before completion of the PASTA pathway. Anticipated reasons are:

- The paramedic is no longer contributing towards the clinical care of the patient.
- A change in the clinical state of the patient making the PASTA pathway no-longer appropriate (further details below).
- A stroke mimic condition is clearly identified during the initial hospital assessment and the hospital team determine that it would no longer be appropriate to continue with a care pathway for suspected stroke (further details below).

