Identification of confirmed stroke patients is facilitated by national clinical guidelines and audit which mandate that all stroke patients should be admitted to ASU within 4 hours of hospital arrival, irrespective of the timing or the local service configuration[5, 8]. It is still possible that a small number of stroke patients attended by a study paramedic will not be admitted to the local ASU because of:

- Transfer to a neuroscience centre for possible surgical or neuro-interventional treatment.
- Very quick recovery and discharge.
- Bed availability on the local ASU.
- Death before transfer from the ED to the ASU

In order to reduce the chance of these patients not being located in hospital, participating ambulance services will send a regular site-specific report of all suspected stroke patients admitted by study paramedics, to each participating site. For patients not listed on the site-specific participant eligibility log, hospital research support staff will check the hospital diagnosis assigned. Where the diagnosis is confirmed stroke, other study eligibility criteria will be reviewed and patients approached about the study as appropriate.

Patients whom the paramedic suspected to be suffering a stroke but who received an alternative diagnosis at hospital ('stroke mimics') will not be approached about study enrolment. However, the hospital diagnosis and any receipt of thrombolysis will be recorded to provide health economic context for the intervention. A site specific 'stroke mimic log' will

be maintained which will not contain patient identifiable material. Any study paperwork (e.g paramedic study documentation) generated by stroke mimic patients will be retained in the local investigator site file.

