*Estimation of consequences for resource use of an enhanced paramedic roles resulting from improved stroke outcomes:*

Data on the use of NHS inpatient resources used will be collected for patients in both arms of the trial. This data will be comprised of brain imaging modality, provision of thrombolysis and length of stay in hospital. In addition, data about community rehabilitation therapy, social service involvement and non elective episodes of secondary care post discharge will also be collected. This information will be collected as part of the study day 1/2 and day 90 data collection points.

Unit costs will be derived from routine sources for NHS and social care. The costs of providing the PASTA pathway for stroke mimic patients will be included within the economic evaluations but also presented separately. This will represent an economic worst case scenario because costs will be added but it will be assumed that there is no benefit (or harm) to these individuals. If the intervention still appears cost-effective in this scenario then the trial conclusions would be strengthened.

*Missing resource use data:*

Where there is data missing about post acute resource usage, essential items will be imputed from data present in the study for similar patients as defined by age, stroke severity and 3 month outcome[33]. Sensitivity analysis will quantify the degree of bias introduced by imputation.

*Sensitivity Analyses:*

Sensitivity analyses will be conducted on key parameters and assumptions contributing the estimates of cost-effectiveness. They will be designed to estimate the robustness of the findings and to provide additional information to decision makers. For example, how estimated cost-effectiveness is affected by assumptions about the extent of the resource and financial burden on ambulance services that result from paramedics performing an enhanced role.

*Long-term economic evaluation:*

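### The economic worst case in section 20 leaves out one group of PASTA deliveries: confirmed strokes that the paramedic judged within 4 hours and the hospital later timed beyond 4 hours

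*Protocol*

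**What the plan says.** Section 11 sets two rules with two different clocks. The pathway is delivered to adults with suspected stroke who are "Within 4hrs of last known to be without new stroke symptoms", as judged by the paramedic. Patients are approached for enrolment only if a hospital specialist diagnoses stroke and they are "Within 4 hours of stroke onset (onset time determined by the hospital stroke team) when assessed by the study paramedic". Section 12 repeats the second rule for the record review.

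Section 12 defines mimics by diagnosis alone: "Patients whom the paramedic suspected to be suffering a stroke but who received an alternative diagnosis at hospital". They are not enrolled, but for them "the hospital diagnosis and any receipt of thrombolysis will be recorded to provide health economic context for the intervention", in a log without identifiers. Objective 3 in section 6.2 uses the same definition.

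Section 20 then states: "The costs of providing the PASTA pathway for stroke mimic patients will be included within the economic evaluations", with a separate presentation as well. It continues: "This will represent an economic worst case scenario because costs will be added", on the assumption that these patients neither gain nor lose. It adds that the trial's conclusions would be strengthened if PASTA still looked cost-effective. No other group outside the participants is named for pathway costing.

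**The concern.** The two clocks will sometimes disagree, and the protocol expects this. Section 13 collects the paramedic's onset time and the stroke team's onset time as separate items, and section 10.1 has the paramedic ask the hospital for feedback on the onset estimate. A patient whose stroke is confirmed but whose onset is moved beyond 4 hours has used paramedic time on the pathway, and yet falls outside both groups that section 20 costs.

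At stake are the cost side of the primary economic result (cost per additional patient thrombolysed) and the cost per QALY. Control patients generate no PASTA cost, so leaving out a class of PASTA deliveries can only lower the incremental cost. It also weakens a specific inference. Section 20 argues that surviving the worst case strengthens the conclusion, which requires that the no-benefit deliveries are all in the sum.

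**Working it through.** **Step 1: sort the PASTA deliveries by the protocol's own rules.** A delivery requires the paramedic's judgement of onset within 4 hours.

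| Hospital finding | Participant? (s.11) | Mimic? (s.12) | Pathway cost named in s.20? |
|---|---|---|---|
| Stroke, onset within 4 h | Eligible | No | Yes, through participants |
| Alternative diagnosis | No | Yes | Yes, added for mimics |
| Stroke, onset beyond 4 h | No | No | No |

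The third row is the gap. Eligible patients who are not enrolled do not form a further gap of this kind, because they belong to the first row, whose unit cost the participants supply.

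**Step 2: direction.** Under the assumption section 20 makes for mimics (cost added, no benefit or harm), adding the third row raises intervention cost and leaves control cost unchanged. The omission is one-sided.

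**Step 3: size.** The plan gives no figure for the third row, so there is nothing to reproduce and no size can be derived. What follows is illustration only. Let r be the share of PASTA-treated confirmed strokes that the hospital times beyond 4 hours; r is an assumption. For N eligible strokes that received PASTA, the uncosted deliveries are N × r/(1 − r).

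| r (assumed) | N = 100 | N = 432 (intervention target, s.18) |
|---|---|---|
| 2% | 2.0 | 9 |
| 5% | 5.3 | 23 |
| 10% | 11.1 | 48 |
| 20% | 25.0 | 108 |

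For example, 432 × 0.10/0.90 = 48. The last column supposes that all 432 received PASTA and that every eligible patient enrolled.

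**Step 4: effect on the primary economic ratio.** Let c be the cost of one delivery. With the postulated change from 0.43 to 0.53 (section 18), each eligible stroke yields 0.10 additional patients thrombolysed. Delivery to eligible strokes alone then contributes c/0.10 = 10c per additional patient thrombolysed. The omitted deliveries would add [r/(1 − r)] × c/0.10:

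- r = 2%: 0.20c
- r = 5%: 0.53c
- r = 10%: 1.11c
- r = 20%: 2.50c

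These are upper figures for each r, because they charge a full c even when the pathway is stopped early. They concern only the pathway-delivery part of cost. Training, inpatient and community costs are not touched.

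**The case against.** Four objections carry weight.

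- **The patients are not invisible.** Section 12 has staff review all confirmed strokes and keep an eligibility log, and ambulance services report every suspected stroke brought in by a study paramedic. Under section 10.1 one copy of the PASTA form stays at the hospital and "a further copy will be returned to the ambulance service". This stands, and it makes the remedy cheap. But being countable is not the same as being costed, and no sentence says these records will be used for this purpose.
- **Worst case may describe only how mimics are treated**, as cost without benefit. That is a fair reading of the phrase. The next step, that the conclusion is strengthened if PASTA survives the scenario, still needs the remaining no-benefit deliveries to be included.
- **Section 20 plans sensitivity analyses on the burden on ambulance services.** These could absorb extra activations, but the text does not mention this group.
- **The pathway may be cut short.** Before CT a hospital clinician confirms likely stroke within the previous 4 hours (section 10.1). That lowers the cost per case. Information gathering, pre-notification and handover will usually have happened already.

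Figure 2, on patient identification, is not shown, and a separate analysis plan may exist. Neither changes what section 20 says.

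A reader might also infer three stronger points that the document does not support:

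- **That thrombolysis given late to this group goes unseen.** A patient beyond 4 hours at paramedic assessment has under 30 minutes left to the 4.5-hour limit, against a median door-to-treatment time of 54 minutes (section 5). The set is close to empty.
- **That mimic cost is inflated because mimics are logged at any onset time and without consent, while participants are a consented 4-hour sample.** Section 20 costs delivery of PASTA to mimics, which section 11 already limits to the paramedic's 4 hours, and retained forms identify those cases. No passage divides mimic cost by consented participants.
- **That the omitted group can be expressed as a share of all activations using the 20% mimic figure.** Section 10.1 gives that figure for FAST-positive patients, whereas PASTA can also be triggered by other focal symptoms.

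**Conclusion.** The point holds in a narrow form. Confirmed strokes given PASTA and then timed beyond 4 hours by the hospital are not costed in section 20, so the scenario described there is not the worst case. Under the section's own no-benefit assumption, the error can only favour PASTA.

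The size cannot be derived from the document. It depends on the re-timed share and on how much of the pathway is delivered before it is stopped. For an assumed share of 2% to 20%, roughly 2 to 25 deliveries per 100 eligible strokes are missing. Since the paramedic leaves within 15 to 30 minutes of hospital arrival, the cost per case is limited and the effect on the ratio is probably small.

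The primary clinical comparison is not affected by this point, because the hospital-timed window applies alike to both arms.

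**What to change.** In section 20, state that the PASTA pathway will be costed for every non-enrolled class of activation: stroke mimics, and confirmed strokes outside 4 hours by the hospital's onset time. Take the counts from the PASTA forms, cross-checked against the ambulance report and the eligibility review in section 12. Add one class to the existing non-identifiable log for these strokes. If this is not done, delete the statement that the mimic costing is a worst case and the inference drawn from it.

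The cost is minor log work, a count of forms already returned and a sentence in section 20. The reported cost of PASTA may become slightly less favourable. No extra patients, visits or consent contacts are needed, and the delivery and enrolment criteria stay as they are.

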## 12. Participant identification, recruitment and consent

Patients will be identified, recruited and consented to take part in this study after arrival at hospital and when the thrombolysis treatment assessment has been completed. There will be no study enrolment process in the pre-hospital setting. The purpose of the study is to demonstrate that the PASTA pathway can expedite the clinical delivery of a treatment which is already known to be effective in reducing future disability, but must be administered rapidly (thrombolysis). A formal research consent process performed by study paramedics or the admitting hospital team would delay hospital admission, brain imaging and / or thrombolysis treatment. Due to the time-dependent effect of thrombolysis, even a short delay could reduce the impact of the PASTA pathway. As the pathway does not involve a new treatment or technology but is attempting to expedite an existing hospital care process using a structured clinical assessment performed by paramedics, the risk of harm to intervention patients is low. Patients will still only receive thrombolysis treatment following review by a stroke specialist. Although they will not provide study information to patients, as per usual clinical practice, paramedics will explain to patients about possible care processes which may occur in hospital.

In order to identify study eligible patients, hospital research support staff will systematically review the ambulance and hospital records of all admitted patients with a confirmed hospital specialist diagnosis of stroke. From the records and using the identification numbers of paramedics involved in the study, staff will identify those patients who travelled with a study paramedic, aged over 18 years and were assessed by the paramedic within 4 hours of the stroke onset time (onset time as determined by the hospital stroke team). Patients meeting these enrolment criteria will subsequently be approached about taking part in the study.

Ideally, approach of patients will take place during their inpatient stay such that a timely discussion about the study can be held. However, some patients are discharged very early after admissions and should identification of an eligible patient occur after discharge from hospital, a postal invitation to take part in the study will be used.

A site-specific participant eligibility log will be maintained. The participant eligibility assessment process is shown in figure 2.

Identification of confirmed stroke patients is facilitated by national clinical guidelines and audit which mandate that all stroke patients should be admitted to ASU within 4 hours of hospital arrival, irrespective of the timing or the local service configuration[5, 8]. It is still possible that a small number of stroke patients attended by a study paramedic will not be admitted to the local ASU because of:

- Transfer to a neuroscience centre for possible surgical or neuro-interventional treatment.
- Very quick recovery and discharge.
- Bed availability on the local ASU.
- Death before transfer from the ED to the ASU

In order to reduce the chance of these patients not being located in hospital, participating ambulance services will send a regular site-specific report of all suspected stroke patients admitted by study paramedics, to each participating site. For patients not listed on the site-specific participant eligibility log, hospital research support staff will check the hospital diagnosis assigned. Where the diagnosis is confirmed stroke, other study eligibility criteria will be reviewed and patients approached about the study as appropriate.

Patients whom the paramedic suspected to be suffering a stroke but who received an alternative diagnosis at hospital ('stroke mimics') will not be approached about study enrolment. However, the hospital diagnosis and any receipt of thrombolysis will be recorded to provide health economic context for the intervention. A site specific 'stroke mimic log' will

be maintained which will not contain patient identifiable material. Any study paperwork (e.g paramedic study documentation) generated by stroke mimic patients will be retained in the local investigator site file.

